## 5 CHANGES TO THE STUDY PROTOCOL

This SAP substitutes the evaluation concept (version 2.1). Changes since version 1.0 of the evaluation concept are 1) classification of headache attacks by a physician instead of an algorithm, 2) the change of the primary endpoint headache days after 12 weeks to migraine days after 12 weeks as requested by the regulatory authority (BfArM), 3) the specification of the secondary outcome “severe headache” to moderate/severe headache days, because this is the commonly used one, and 4) the further measurement “concomitant interventions” to “concomitant activities / activities”, because the questions include both activities recommended by the app and activities that are not included but might be used concomitantly.

## 6 OUTCOMES

Data for the DiGA study will be collected at different time points (baseline (for 4 weeks before randomization), 4 weeks, 8 weeks, and 12 weeks), for details see Table 1. Scale properties, range of possible values, and interpretation of values for each outcome are given in Table 2.

**Table 1.** Data collection

| Time (week)                                           | Baseline
4 weeks | Before
randomization | Diary
12 weeks
DIGA study | 4
weeks | 8 | 12 | + 12 weeks for
follow-up study # |
|-------------------------------------------------------|---------------------|-------------------------|---------------------------------|------------|---|----|------------------------------------------------|
| Eligibility criteria                                  | x                   | x                       |                                 |            |   |    |                                                |
| Episodic migraine or
chronic migraine
diagnosis | x                   | x                       |                                 |            |   |    |                                                |
| Participant characteristics                           | x                   | x                       |                                 |            |   |    |                                                |
| Migraine days                                         | x                   |                         | x                               |            |   |    |                                                |
| Headache days                                         | x                   |                         | x                               |            |   |    |                                                |
| Moderate/severe headache
days                      | x                   |                         | x                               |            |   |    |                                                |
| HIT-6                                                 |                     | x                       |                                 |            |   | x  | x                                              |
| HMSE-G-SF                                             |                     | x                       |                                 |            |   | x  | x                                              |
| HALT-30                                               |                     | x                       |                                 |            |   | x  | x                                              |
| Migraine specific health
literacy                  |                     | x                       |                                 |            |   | x  |                                                |
| Medication use                                        | x                   |                         | x                               |            |   |    |                                                |
| Use of app interventions                              |                     |                         | x                               |            |   |    | x                                              |
| Safety measures                                       |                     |                         |                                 | x          | x | x  | x                                              |

#not part of this SAP

## 6.1 PRIMARY OUTCOME

The primary outcome are the **migraine days per month** (defined as 28 days) after 12 weeks (week 9 to 12). Migraine days will be based on the information in the headache diary. Headache attacks will be classified according to ICHD-3 (criteria B to D) by a physician blinded for the patient's group allocation. A migraine day is defined as a calendar day on which a single or multiple migraine attacks have been reported.

The information necessary for the classification as migraine attack ICHD-3 criteria B to D (see below) will be used based on data of the diary.

The criteria B to D are:

- B. Headache attacks lasting 4-72 hr (untreated or unsuccessfully treated)
- C. Headache has at least two of the following four characteristics:
  - 1. unilateral location
  - 2. pulsating quality
  - 3. moderate or severe pain intensity
  - 4. aggravation by or causing avoidance of routine physical activity (eg, walking or climbing stairs)
- D. During headache at least one of the following:
  - 1. nausea and/or vomiting
  - 2. photophobia and phonophobia

The physician will manually classify the headache attacks based on the raw data of the diary according to ICHD-3 (criteria B to D). Any information which has to be manually added to the analysis dataset will be based on double entry and subsequent comparison to control for data entry errors. In a next step we will compare the results from the manual classification with the M-sense algorithm^3. In case of discrepancies the physician will re-evaluate his/her classification and make a final decision.

The number of migraine days per month is obtained by adding up the number of migraine days within four consecutive weeks (28 days). When the respective information needed for the classification has been sufficiently documented by the patient the headache days will be classified into three categories: 1. migraine days, 2. days with tension type headache, or 3. other headaches (do not meet criteria for migraine days or days with tension type headache). If the respective information provided by the patient is not sufficient for classification, the classification value for this day would be seen as a missing value.

To support a complete documentation technically, a daily headache question with a dichotomous value (headache yes/ no) has been implemented in both app versions (M-sense Migräne app and control app). This question will be shown every day when the app is opened for the first time. The app also motivates patients to open the app daily and document their headache attacks. The headache diary records the time period of attacks, as well as the pain characteristics and attendant symptoms for every documented headache attack. The choice of the primary outcome was requested by the regulatory body (BfArM) based on the Guidelines of the International Headache

Society for controlled trials on preventive (pharmacological) treatment of episodic migraine and preventive treatment of chronic migraine in adults.

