**Figure 2. Screenshots of the study app**

a) The comprehensive **headache diary** allows a real time tracking of headache occurrences, including headache characteristics, attendant symptoms and experienced pain intensity levels. These headache entries are automatically classified by the M-sense headache classification algorithm, a digitalized version of the ICHD-3-based headache classification. The algorithm allocates single headache attacks to the phenotypes migraine, tension-type headache (TTH), and unclassified headaches. The validity of M-sense's algorithm was assessed by comparing the classification of single headache attacks performed by the algorithm to the attack classification performed by a certified neurologist specialised in headache medicine. The substantial level of agreement between the neurologist and the algorithm was obtained (unweighted kappa=0.74). Most cases of disagreement were due to inadvertent mistakes of the neurologist as identified in the disagreement validity assessment.

b) The **diary for medication intake** allows users to track intake of their prophylactic and acute pain medication and to receive information on proper intake of medications and the potential hazards of medication overuse.

- c) The **diary for trigger factors** list potential migraine trigger factors, e.g. sleep duration, period, alcohol consumption, stress (for details see Wöber & Wöber-Bingöl, 2011). Through descriptive statistics potential individual triggers can be detected.
- d) The **analysis function and physician report** analyses and visualizes the data entered into the app, including headache types, monthly headache occurrence, monthly average pain intensity and frequency of headaches, trigger statistics, headache distribution by time-of-day, day-of-week, and days-in-month and medication intake in weekly and monthly reports, as well as via the in-app calendar. This helps users to self-monitor the course of the disease and their medication intake. The report can be used to facilitate patient-physician communication.
- e) For the **personalized education about disease- and trigger management** the M-sense Migräne app includes 20 individualized knowledge lessons about migraine (e.g. symptoms, trigger factors and causes) and its treatment options (acute and preventive).

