### 10.2 Baseline and informed consent

With the access code the control app can be used for a 28 days baseline assessment as recommended for migraine studies. The participants will receive privacy information within the app and their electronic consent will be obtained.

The data will be used at the end of the baseline phase to assess the eligibility for the study. Close to the end of the baseline phase the migraine diagnosis will be confirmed in a video consultation by a physician, the main study eligibility will be checked and the informed consent will be obtained. The informed consent includes general information about the study, inclusion and exclusion criteria, the course of the study, the study tasks, data gathering and data use, the risks, privacy, time commitment, and the withdrawal procedures. Eligible patients who provided informed consent will receive a study code from the physician. After they completed the baseline phase the control app checks the in-app eligibility criteria (migraine  $\geq 3$ , filling in of the diary, no medication overuse). All other eligibility criteria will be checked by the physician. Participants who do not fulfill eligibility criteria will be offboarded by the app and their data will be deleted.

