## 2 AIM OF THE TRIAL

The aim is to evaluate the effectiveness of the M-sense Migräne app in reducing migraine days in patients with episodic migraine and chronic migraine compared to patients in a waiting list control group who have no access to the app intervention features.

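### Under the 4-72 hour criterion a documented attack longer than 72 hours adds no migraine days, so the primary endpoint runs backwards for such attacks

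*Combined protocol and SAP*

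**What the plan says.** SAP 6.1 defines the primary outcome in two steps. Attacks are classified first: "The physician will manually classify the headache attacks based on the raw data of the diary according to ICHD-3", criteria B to D. Days are then counted: "A migraine day is defined as a calendar day on which a single or multiple migraine attacks have been reported". Criterion B is given as "Headache attacks lasting 4-72 hr (untreated or unsuccessfully treated").

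A sufficiently documented headache that is not migraine goes to tension-type headache or to "other headaches (do not meet criteria for migraine days or days with tension type headache"). Duration is available, because "The headache diary records the time period of attacks". After comparison with the app's algorithm the physician may revise a classification, but no criterion other than B to D is named.

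Three other places bear on the point:

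- SAP 10.4.3 replaces a headache day with a migraine day, in both arms and at baseline, only when the information needed for classification was not documented.
- SAP 6.2 defines moderate/severe headache days by more than 4 hours and a pain score of at least 4, with no upper limit on duration.
- Entry requires at least 3 migraine days in the 28-day baseline. Evaluation concept 10.2 says: "After they completed the baseline phase the control app checks the in-app eligibility criteria". Section 7.1 a) describes diary entries in the M-sense app as "automatically classified by the M-sense headache classification algorithm, a digitalized version of the ICHD-3-based headache classification".

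**The concern.** The duration criterion has an upper bound, and the endpoint counts calendar days of qualifying attacks. Together they make the score discontinuous at 72 hours. Just below the bound, an attack scores every calendar day it touches. Just above it, the attack scores nothing, although the patient has been ill for longer. A true improvement that brings an attack back under 72 hours is recorded as more migraine days, and a deterioration past 72 hours as fewer.

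This affects the only confirmatory endpoint. It also affects the responder outcome, which uses the same count, and the baseline covariate in the ANCOVA. The plan is not consistent on the point: a fully documented 80-hour attack with migraine features scores zero, while a headache day with nothing recorded about its features is scored as migraine. The same 80-hour attack can count in full as moderate/severe headache days.

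**Working it through.** **The plan's own figure.** SAP 7 assumes a difference of 1.27 days, SD 4.20, two-sided alpha 5% and power 80%. The t-test calculation gives 172.65 per group, rounded up to 173, with power 0.801 at 173. The stated sample size reproduces and is not in dispute; 1.27 is used below only as a yardstick.

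**Score of one attack under the written rule.** Assume C and D are met. An attack of L hours starting at clock hour h (0 to under 24) touches ceil((h + L)/24) calendar days. These count as migraine days only if L is between 4 and 72.

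| Duration (h) | Calendar days touched | Migraine days scored |
|---|---|---|
| 96, 84, 80 or 73 | 4-5 | 0 |
| 72 or 60 | 3-4 | 3-4 |
| 48 | 2-3 | 2-3 |
| 24 | 1-2 | 1-2 |

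Shortening from above 72 hours to 48-72 hours therefore moves the score from 0 to between 2 and 4. That is 2/1.27 = 1.6 to 4/1.27 = 3.1 times the planned difference, in one patient and in the wrong direction.

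**Why nothing else in the SAP repairs it.** The replacement rule in 10.4.3 needs undocumented information, and here the duration is recorded. The discrepancy step in 6.1 gives the physician nothing beyond B to D to apply.

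**Responder example.** Attacks start at 08:00. Baseline: one 80-hour attack, ceil(88/24) = 4 days, plus 4 other migraine days. Weeks 9-12: the attack is cut to 60 hours, ceil(68/24) = 3 days, plus 2 other migraine days.

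- Literal count: 0 + 4 = 4, then 3 + 2 = 5. A 25% increase; non-responder.
- All documented days counted: 4 + 4 = 8, then 3 + 2 = 5. A 37.5% reduction; responder.

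**Size at trial level.** Shift = (net share of app patients with one such crossing minus net share of control patients) x days per crossing. Neither share is in the documents, so this is illustration over an assumed range:

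| Net excess in app arm | 2 days each | 3.5 days each | 4 days each |
|---|---|---|---|
| 2% | 0.04 (3% of 1.27) | 0.07 (6%) | 0.08 (6%) |
| 5% | 0.10 (8%) | 0.18 (14%) | 0.20 (16%) |
| 10% | 0.20 (16%) | 0.35 (28%) | 0.40 (31%) |

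At 3 days each and SD held at 4.20, the remaining difference would be 1.21, 1.12 or 0.97, with power of about 76%, 70% or 57%. If crossings balance between arms, the shift is zero.

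**Entry check.** If the app applied 72 hours literally, two 80-hour attacks starting at 08:00 would give 8 headache days and 0 migraine days, below the threshold of 3. Attacks of 80, 20 and 10 hours would give 3 migraine days and pass.

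**The case against.** The strongest reply is that a score of zero is nowhere stated. SAP 6.1 also speaks of sorting headache days into categories, does not say whether one long episode may be split, and leaves the final decision to a blinded physician who might count such days. It is true that zero follows from the literal attack-level reading. But discretion with no criterion other than B to D is not a rule, and if it were used, the confirmatory endpoint would rest on an unwritten convention.

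Second, B to D are the published criteria and the regulator requested the outcome. That is a good reason to keep the literal count in the report, and the fix does so.

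Third, the rule is the same in both arms, classification is blinded, and the likely bias is towards no benefit, so it should not produce a false claim for the app. This also stands. It does not help a trial planned at 80% power with no allowance for dropouts. Headache days and moderate/severe headache days would pick up these attacks, but only as exploratory outcomes.

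Fourth, counting every day without limit would let a diary entry that was never closed add many migraine days. This is a fair point and shapes the fix.

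A reader might infer three stronger things:

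- *That patients with prolonged attacks will be screened out.* The documents say only that the algorithm is based on ICHD-3; how it handles attacks over 72 hours is not shown. Screen-out would need a literal 72-hour limit and fewer than 3 other qualifying days. It would alter who enters, not the randomised contrast.
- *That the chronic stratum is hit hardest.* Nothing in the documents says prolonged attacks are commoner there.
- *That 6% to 28% of the effect is lost.* Those figures rest on assumed shares and a swing of 3.5 days, near the maximum. Attacks can cross 72 hours in either direction in either arm; an attack cut to 24 hours scores 1-2, and one prevented altogether scores 0 before and after.

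**Conclusion.** The point holds as a defect in the counting rule. Under SAP 6.1 as written, a documented attack over 72 hours that meets C and D scores 0 on its 4 or more calendar days and would score 2 to 4 if shortened to 48-72 hours. The primary endpoint and the responder outcome run backwards for these attacks, and the rule sits badly beside SAP 6.2 and 10.4.3.

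This requires that the shortened attack still meets C and D and lasts 4 to 72 hours. The effect on the trial result is unknown, because the frequency is not given and only the net between-arm difference in crossings matters. The direction is probably towards no benefit, on the assumption that the app shortens attacks. Exclusion at baseline is possible but not established. The sample size is unaffected. The change is worth making because it is cheap and concerns the sole confirmatory test.

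**What to change.** Before unblinding:

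1. Add to SAP 6.1 that calendar days belonging to an attack that meets C and D and lasts more than 72 hours count as migraine days, identically in both arms, at baseline and in weeks 9-12. Limit this to days with a documented headache, for example confirmed by the daily headache question, so that unclosed entries add nothing. Say how a day inside the attack with no answer to that question is treated.
2. Put the same line in the physician's classification instruction, and apply the count to the responder outcome.
3. Report the literal 4-72 hour count as a sensitivity analysis, with the number of attacks over 72 hours by arm and period.
4. Establish from the algorithm's specification how it treats such attacks, and reconcile the baseline check of at least 3 migraine days with the SAP definition. The data of people who fail that check are deleted, so this cannot be recovered later.

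The cost is one or two sentences, one instruction line and one extra analysis run on diary data already collected. The main count departs from literal criterion B, which the sensitivity analysis covers. Any change to the app's own check should be costed separately, since the control app is a configuration of a CE-marked device.

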## 6.2 SECONDARY OUTCOMES

Secondary outcomes based on the diary within the app:

- Migraine days per month (months defined as 28 days) week 1 to 4 and week 5 to 8.
- Headache days per month (months defined as 28 days) week 1 to 4, week 5 to 8, and week 9 to 12. The headache days are defined as the number of days on which headaches have been documented by the patient in the diary. The number of headache days per month is then obtained by adding up the number of days on which headaches have been reported within four consecutive weeks (28 days).
- Moderate/severe headache days (defined as a headache that is longer than 4 hours and is accompanied with a pain severity of at least 4, as reported on the in-app 11-point numeric rating scale (NRS) for pain, 0=“kein Schmerz” to 10=“stärkster Schmerz”) per months (defined as 28 days) after 12 weeks (week 9 to 12). Furthermore, we will analyze week 1 to 4 and week 5 to 8.
- Treatment responder defined as at least a 30% reduction in migraine days per month (defined as 28 days) after 12 weeks (week 9 to 12) compared to baseline. Study dropouts (see 10.4 for definition) will be handled as non-responders in the analysis.
- Drug consumption for acute pain treatment includes: a) days with medication for acute pain, and b) days with triptane use. This is documented in the daily medication diary (week 1-12).

Secondary outcomes based on questionnaires within the app:

- Migraine specific quality of life measured with the 6-item Headache Impact Text (HIT-6) over the last 4 weeks after 12 weeks. For the analyses we will aggregate the single items in an index using the The PRO CoRE™ Software and follow the “HIT-6: A User's Guide eManual” of the license holder Optum.
- Self-efficacy measured with the 6-item short form of the German language adapted headache management self-efficacy scale (HMSE-G-SF) over the last 4 weeks measured after 12 weeks.

- Headache attributed burden such as disability and headache attributed lost time is measured with the 5-item Headache-Attributed Lost Time indices (HALT-30^10, official German translated Version) over the last 30 days after 12 weeks. The HALT-30 was developed as part of "The Global Campaign against Headache" with support from the World Health Organization. The HALT items are fully based on the five MIDAS items with slightly changed wording for more clarity and a shorter retrospective reporting period (30 instead of 90 days). Because of this, the HALT-30 can be viewed as an improvement of the MIDAS and the indices show no changes to the structure and scoring of the well-validated MIDAS.
- Migraine-specific health literacy after 12 weeks (3 items, own development) with the items prophylaxis literacy, disease literacy, trigger literacy on a 4 point Likert-type scale from 1="sehr gut" to 4="sehr schlecht".

### 6.3 FURTHER MEASUREMENTS

- Adherence to the study intervention is only observed in the M-sense Migräne app group and on weekly basis. Being adherent is defined for a patient as using an app feature which is not implemented in the control app, at least one time per week.
- Tracked usage of app features during the 12 weeks is only measured in the intervention group with M-sense Migräne including (a) Headache reporting and attack classification diary; b) Medication intake diary; c) Trigger factors diary; d) Analysis function and physician report; e) Personalized education on disease- and trigger management; f) Relaxation therapy; g) Training module; h) Acute pain therapy. This data will be displayed descriptively.
- Concomitant activities/ activities are documented in both groups (activities recorded in an app diary: mindfulness practice, breathing meditation, autogenic training, muscle relaxation, qigong/tai chi, yoga, nordic walking, cardio-training, fitness course, running, cycling, and swimming) used against headache during the first 12 weeks (activity, and time spent for respective activity). Some of these activities are recommended in the app, others not. We will calculate the number of patients with respective activities.

